### Primary Outcome Measures

The primary outcome measures focus on the efficacy and safety of the device and generally align with standardized definitions reported previously [21, 22].

The primary efficacy outcome measure is the proportion of patients with target lesion primary patency (TLPP) at 6 months. TLPP is defined as freedom from clinically driven target lesion revascularization or target lesion thrombosis measured through 6 months post-procedure, which is the time interval of uninterrupted patency following the study procedure to the next intervention performed on the target lesion, or uncorrectable target lesion occlusion.

The primary safety outcome measure is the proportion of patients without any localized or systemic safety events through 30 days post-procedure that affect the access or venous outflow circuit and result in reintervention, hospitalization, or death (not including stenosis or thrombosis).

### Additional Outcome Measures Assessed

Secondary outcomes will include the proportion of patients with: TLPP at 12 and 24 months; assisted TLPP at 6, 12, and 24 months (defined as the time to loss of assisted primary patency of the target lesion, which is the time from the study procedure to uncorrectable target occlusion); access circuit primary patency at 6, 12, and 24 months (defined as time to loss of primary patency); post-procedure secondary patency outcomes at 6, 12, and 24 months (defined as the interval post-procedure until access circuit abandonment). Additional secondary outcome measures include serious adverse events across the 24 month study period, number of device observations, number of interventions to maintain access circuit patency, number of target lesion re-interventions to maintain target lesion patency, as well as the percentage of patients with device success, procedural success, and anatomic success.

Pending data availability, additional outcome measures will include index of patency function at 6, 12, and 24 months (defined as the time from the initial study procedure to complete access abandonment divided by the number of venous outflow circuit re-interventions to maintain hemodialysis); clinical success (defined as resumption of successful dialysis through existing access for ≥ 1 session post-procedure); functional patency of the access (defined as the ability to support dialysis) at 6, 12, and 24 months. Provided follow-up imaging is collected as part of the standard of care, additional outcome measures will include the incidences of reported stent fractures, migration, and edge stenosis.

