### Statistics

Data will be organized into two analytical sets: an intent-to-treat (ITT) analysis set and a per-protocol (PP) analysis set. The ITT analysis set will include all patients enrolled in the study and will be considered the primary analysis set for all safety and efficacy outcome measures. The PP analysis set will include all enrolled patients who meet all inclusion and exclusion criteria with no major protocol deviations.

All analyses will be descriptive; no hypothesis testing is planned. Continuous variables will be summarized using mean, standard deviation, median, minimum, and maximum. Categorical variables will be summarized using frequencies and percentages will be reported with their associated confidence intervals. Time-to-event data will be summarized using Kaplan–Meier curves. All data will be analyzed using SAS version 9.4, or later (SAS Institute Inc., Cary, NC).

The sample size of 500 was determined to be sufficient to accurately characterize use of WRAPSODY in real-world practice based on clinical consensus of the study’s principal investigators. An interim analysis is not currently planned.

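### Assisted TLPP ends only at an occlusion that cannot be corrected, so a target lesion that thromboses and is reopened still counts as assisted-primary patent

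*Protocol article*

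**What the plan says.** The protocol article describes three tiers of patency.

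- **TLPP** (Primary Outcome Measures) is "freedom from clinically driven target lesion revascularization or target lesion thrombosis measured through 6 months post-procedure". The same sentence also describes it as an interval that runs to "the next intervention performed on the target lesion, or uncorrectable target lesion occlusion". It is primary at 6 months and secondary at 12 and 24 months.
- **Assisted TLPP** (Additional Outcome Measures Assessed), reported at 6, 12 and 24 months, is "time to loss of assisted primary patency of the target lesion, which is the time from the study procedure to uncorrectable target occlusion".
- **Secondary patency** (same section), reported at the same times, is "defined as the interval post-procedure until access circuit abandonment".

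The Statistics section states: "All analyses will be descriptive; no hypothesis testing is planned". Percentages are to carry confidence intervals, and time-to-event outcomes are to be shown as Kaplan–Meier curves.

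**The concern.** Assisted primary patency sits between the other two tiers. Its name suggests that it forgives interventions that keep an open lesion open, while loss of the lumen still ends it. The stated definition forgives more. A complete thrombosis of the target lesion is not an event if it can be reopened, however often it recurs. The top tier names thrombosis as a loss, and the middle tier drops it without comment.

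This matters because the registry tests nothing, so the reported proportions and curves are its conclusions. The section Expected Gain of Knowledge anticipates patency that compares well with other covered stents and expects the results to inform decision-makers. An assisted-primary figure that ignores reopened thromboses cannot be set beside one that counts them, and the difference favours the device.

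**Working it through.** The article states no figure to reproduce. The check is to follow each possible course of the target lesion through the definitions.

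| Course of the target lesion | TLPP | Assisted TLPP as written | Assisted TLPP if thrombosis ended it |
|---|---|---|---|
| Stenosis treated while the lesion is open | lost | kept | kept |
| Thrombosis, reopened, no later uncorrectable occlusion | lost | kept | lost |
| Occlusion that cannot be corrected | lost | lost | lost |

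Only the second row differs between the last two columns.

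**Size.** Take complete follow-up to time t. Let U be the share of patients with an uncorrectable target occlusion by t. Let S be the share with a corrected target-lesion thrombosis or occlusion and no uncorrectable one by t.

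- As written: 1 − U.
- With thrombosis counted: 1 − (U + S).
- Difference: S.

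Every patient in S has also lost TLPP, so S cannot exceed total TLPP loss at t.

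**Illustration.** The article gives no thrombosis rate, so these values of S are assumptions, applied to its 500 patients:

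- S = 2%: 0.02 × 500 = 10 patients, 2 points
- S = 5%: 0.05 × 500 = 25 patients, 5 points
- S = 10%: 0.10 × 500 = 50 patients, 10 points

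**Check against the article's own figures.** The Introduction reports primary patency in the first-in-man study of 97.7% at 6 months and 84.6% at 12 months. Loss from all causes was therefore 100 − 97.7 = 2.3% and 100 − 84.6 = 15.4%. If the registry behaved the same way, and if that measure matches TLPP, S could not exceed 2.3 points at 6 months or 15.4 points at 12 months. Of the illustrative values, only 2% would then be possible at 6 months. That study had 46 patients, and the registry's entry criteria are deliberately broad, so registry rates may differ.

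**Scale against sampling error.** Assuming 95% intervals and n = 500, the half-width is 1.96 × √(p(1 − p)/500). At p = 0.85 this is 1.96 × √(0.1275/500) = 3.1 points. At p = 0.75 it is 1.96 × √(0.1875/500) = 3.8 points. An S of 5% would exceed either half-width; an S of 2% would not.

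**The case against.** The strongest defence is that the wording is coherent. The second half of the TLPP definition ends the interval at "the next intervention performed on the target lesion, or uncorrectable target lesion occlusion". Remove the intervention and what remains is, in substance, the assisted definition. Reopening a clot is an intervention, and interventions are what an assisted measure forgives. Nor does any section say that assisted TLPP must end at thrombosis. The statement that definitions "generally align with standardized definitions reported previously" is made for the primary outcomes only, and its sources are not at hand.

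This explains how the wording may have arisen, but it does not settle the point. The first half of the TLPP definition lists thrombosis separately from revascularization, and that event is not carried down. The argument here rests on this contrast and on the word primary in the label, not on an outside standard. Because it is partly a matter of label, renaming alone is an acceptable minimum.

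The rest of the defence limits the finding and stands:

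- A reader might infer that the outcome duplicates the protocol's secondary patency. It does not. That outcome is at circuit level and ends at abandonment; assisted TLPP is at lesion level.
- A reader might infer that thrombosis is hidden. A first target-lesion thrombosis ends TLPP if nothing has ended it earlier, and repeat reopening enters the count of target-lesion re-interventions. What is missing is a patency outcome that shows thrombosis separately from maintenance.
- A reader might infer an overstatement above ten points. Assuming that 15% of lesions thrombose by 12 months and 90% of those are reopened gives 0.15 × 0.90 = 13.5 points. Against the 15.4% all-cause loss in the first-in-man study, nearly every loss would have to be a thrombosis. The product also assumes that no reopened lesion later occludes for good. The documents do not support a figure of that size.

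**Conclusion.** The point holds as a badly fixed definition of one secondary outcome. The article states the rule in full, so this is not a detail left to the full protocol or analysis plan. As written, assisted TLPP measures lesion-level salvage under a primary-assisted label and will read higher than a measure in which thrombosis counts.

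The direction is certain wherever any target-lesion thrombosis is reopened and stays correctable. The size is unknown: it is bounded by S and by total TLPP loss, and the 2 to 10 points above are illustrative only. Neither primary outcome measure is affected. The change is worth making before results are reported, but the point does not threaten the registry's main conclusion.

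**What to change.** Define assisted TLPP as the time from the index procedure to the first thrombosis or occlusion of the target lesion, corrected or not. Interventions on a lesion that is still patent would not count as loss. Keep the present version as an additional estimate named *target lesion secondary patency*.

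The cost is one definition, one label and no new visit, but the data need checking. Table 2 collects subsequent circuit interventions at follow-up and does not say whether the lesion was thrombosed or patent each time. TLPP needs that information only up to its first loss. The revised outcome also needs it afterwards, for example when an early maintenance procedure is followed by a thrombosis. The status must therefore be taken from the record of each subsequent target-lesion intervention. If it cannot be recovered, the present outcome should at least be renamed. The assisted figure will become less favourable.

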## Introduction

Hemodialysis is the most common form of kidney replacement therapy, accounting for nearly 90% of all dialysis methods [1, 2]. The success of hemodialysis requires continuous function of a vascular access that is traditionally accomplished through the creation of an arteriovenous fistula (AVF) or implanting an arteriovenous graft (AVG) [3, 4]. However, complications such as stenosis and/or occlusion are a leading cause of failure in the AVF and AVG, which can interfere with the ability of patients to undergo hemodialysis, resulting in potentially increased morbidity and life-threatening consequences [4–6].

Treatment options to adequately manage dysfunctional vascular access due to stenosis/occlusion are associated with limited patency. Surgery may assist with achieving extended patency of the access circuit, however, high rates of morbidity due to trauma preclude it from becoming a commonly employed treatment strategy and is instead reserved for non-salvageable vascular accesses [7–9]. A common endovascular alternative for the clinical management of venous stenosis/occlusion includes use of percutaneous transluminal angioplasty (PTA) [7, 10–14]. However, patency of PTA can vary widely, with average reported cumulative primary patency rates of 61% and 47% at 6 and 12 months, respectively [15], which often requires re-intervention(s) to maintain patency. Within the past 30 years, covered stents have emerged as an alternative to PTA to maintain patency of the hemodialysis access circuit [16]. The proposed advantages of covered stents over PTA are their stable and relatively inert matrix to support endothelialization coupled with their structural rigidity to help maintain patency of the circuit [17]. However, even with early covered stents, patency rates have been reported to decline over time with one study reporting approximately 70% of patients requiring re-intervention within one year of placement [18]. As a result, there has been an impetus to continue to innovate covered stents to improve patency of vascular access for hemodialysis.

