The WRAPSODY™ Cell-Impermeable Endoprosthesis, a novel covered stent, was developed to help improve long-term vascular access. The device is a self-expanding endoprosthesis composed of a single nitinol wire encased between layers of fluoropolymer that helps to reduce stenosis and thrombus formation. A preclinical study that examined rates of stenosis following placement of the WRAPSODY device versus a conventional covered stent found that the device was associated with significantly lower rates of stenosis (2.1% vs. 10.3%, *p* = 0.009) [19]. Findings from the first-in-man study of the WRAPSODY device, that included 46 patients with access circuit stenosis treated with the device, demonstrated primary patency rates of 97.7% and 84.6% at 6 and 12 months, respectively, [20]. Based on the results of the first-in-man study in 2020, the WRAPSODY device received CE Mark approval.

Despite the promising efficacy outcomes associated with the WRAPSODY device [19, 20], there is an unmet need for real-world data describing clinical outcomes associated with the device, particularly in a large patient population. To help address this need, we describe the design of a prospective, multicenter, post-market, observational study (the WRAP Registry) that will document real-world data for safety and efficacy outcomes following use of the WRAPSODY device in 500 patients.

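### The index of patency function has no value for a patient without a re-intervention, which on the article's own figures is probably more than half of patients at 6 months

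*Protocol article*

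**What the plan says.** The article's section Additional Outcome Measures Assessed introduces the measure as conditional: "Pending data availability, additional outcome measures will include index of patency function at 6, 12, and 24 months". It then gives the formula: "time from the initial study procedure to complete access abandonment divided by the number of venous outflow circuit re-interventions to maintain hemodialysis".

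The denominator counts re-interventions only. The index procedure is not counted, nothing is added to the count, and no rule covers a count of zero. The numerator ends at complete abandonment of the access. The text does not say that time is cut at 6, 12 or 24 months for an access still in use.

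The Statistics section adds nothing specific to the index. For continuous measures it says: "Continuous variables will be summarized using mean, standard deviation, median, minimum, and maximum". Time-to-event data go to Kaplan–Meier curves, and all analyses are descriptive.

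**The concern.** A ratio with a count in the denominator fails when the count is zero, and here zero is the result the device is meant to produce. If patients without a value are left out of the mean and median, the index describes only those who needed re-intervention while carrying a label that suggests the whole cohort. The omitted courses are mostly favourable, so the summary would tend to understate the device's performance.

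The alternative is a repair chosen after the data are seen. Replacing a zero count by one, for example, gives a patient with no re-intervention the same value as a patient with one over the same time, so the index no longer separates them.

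The numerator raises a second difficulty. Table 1 excludes patients whose access is expected to be given up within 6 months, so abandonment by the first time point should be uncommon. For most patients the time to abandonment will then not have been observed when the index is due.

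**Working it through.** The article states no expected value for the index, and 500 does not come from a formula ("The sample size of 500 was determined to be sufficient to accurately characterize use of WRAPSODY in real-world practice", by clinical consensus). There is therefore no figure to reproduce. The check has three steps.

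**1. The formula as stated.** Let T be the time to abandonment and k the number of venous outflow circuit re-interventions. With T = 180 days for illustration:

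| k | T / k (as stated) | T / (1 + k) |
|---|---|---|
| 0 | undefined | 180 |
| 1 | 180 | 90 |
| 2 | 90 | 60 |
| 3 | 60 | 45 |

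**2. How many patients have k = 0.** The number without a value is 500 × P(no re-intervention). No circuit re-intervention rate is given, so three figures from the Introduction serve as proxies:

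- First-in-man study of the device (46 patients): "demonstrated primary patency rates of 97.7% and 84.6% at 6 and 12 months, respectively".
- Balloon angioplasty: "average reported cumulative primary patency rates of 61% and 47% at 6 and 12 months, respectively".
- Early covered stents: "approximately 70% of patients requiring re-intervention within one year of placement", so about 30% without re-intervention at 12 months. To bring this back to 6 months I assume a constant hazard: 0.30^0.5 = 0.548.

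| Proxy | 6 months: no value | 12 months: no value |
|---|---|---|
| First-in-man | 500 × 0.977 = 488.5 (about 488) | 500 × 0.846 = 423 |
| Angioplasty | 500 × 0.61 = 305 | 500 × 0.47 = 235 |
| Early covered stents | 500 × 0.548 = 274 | 500 × 0.30 = 150 |

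At 6 months every proxy puts more than half of 500 without a value. At 12 months this holds only for the first-in-man figure. The article gives no figure from which to estimate 24 months. Enrolment is described as up to 500; with fewer patients the counts shrink in proportion.

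**3. When the statement that more than half lack a value at 6 months would fail.** Under a Poisson model with rate r per patient-year, P(k = 0) at 6 months is exp(−0.5r). This equals 0.5 at r = ln 2 / 0.5 = 1.39. Circuit re-interventions would have to exceed about 1.39 per patient-year.

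These counts reflect the zero denominator alone. If the numerator is also read literally, patients with a re-intervention but an access still in use lack a value too. That addition cannot be sized, because the article gives no abandonment rate.

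**The case against.** The strongest reply is that this is a low-tier outcome, descriptive and conditional on data, and that an analysis plan not shown here may state how zeros and accesses still in use are treated. The low tier is true and limits the importance of the point. The second part does not remove it: the article gives an explicit formula, and a plan could give patients with no re-intervention a value only by changing that formula.

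The proxies are also imperfect. They are patency or re-intervention figures from other settings, one of them from 46 patients. Re-interventions anywhere in the venous outflow circuit can outnumber those at the target lesion, so the number without a value may be smaller than shown. This stands, and the counts should be read as rough.

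Three stronger readings are tempting, and the article does not support them:

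- *The index exists only for patients who were re-intervened and also lost the access.* This follows from a strictly literal numerator. Reporting at fixed landmarks suggests that time may be meant to stop there. Truncation is unstated, not excluded. With it, the angioplasty proxy leaves 500 − 235 = 265 patients with a value at 12 months, a majority.
- *The patients without a value are the best outcomes.* Mostly, but an access abandoned without any re-intervention also has a zero count.
- *The separate count outcomes, such as "number of interventions to maintain access circuit patency", are biased by unequal follow-up.* The article only names these counts. It does not say that follow-up time is ignored, and it gives no attrition figure. An analysis plan may well specify rates.

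**Conclusion.** The definition is wrong as written. It gives no value when there are no re-interventions, and it relies on an abandonment time that is unobserved for any access still in use at the time point. On the article's own figures, taken as rough proxies, about 274 to 488 of 500 patients would have no value at 6 months and about 150 to 423 at 12 months. The lower 6-month figure assumes a constant hazard over the first year.

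That patients without a value would be dropped is an inference; the article does not say what would be done with them. If they are dropped, the summary describes re-intervened patients only. The consequence is confined to one additional descriptive outcome. Neither primary outcome, 6-month target lesion primary patency or 30-day safety, depends on it.

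**What to change.** At each landmark t (6, 12 and 24 months), define the index as the time from the procedure to the earlier of abandonment or t, divided by one plus the number of venous outflow circuit re-interventions in that time. Summarise it per patient among those followed to t or to abandonment.

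The restriction on follow-up is needed. If time simply stopped at last contact, a patient with no re-intervention who left at month 2 would score 2 / 1 = 2 months. A patient followed for 6 months with two re-interventions would score 6 / 3 = 2 months as well. Early censoring would then count as poor patency.

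For all patients, including those censored early by death, withdrawal or loss to follow-up, also report the cohort-level ratio: total access time in use divided by total re-interventions, with a robust confidence interval. State beside the per-patient summary how many patients contribute to it.

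The cost is wording in the definition and the analysis text. Follow-up already covers dialysis status and later interventions, as available. Secondary patency, which ends at abandonment, needs the abandonment date anyway, although Table 2 does not list that date as an item of its own, so its capture should be confirmed. The downside is that values with the added one are not directly comparable with indices computed without it; the report should say so.

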### Statistics

Data will be organized into two analytical sets: an intent-to-treat (ITT) analysis set and a per-protocol (PP) analysis set. The ITT analysis set will include all patients enrolled in the study and will be considered the primary analysis set for all safety and efficacy outcome measures. The PP analysis set will include all enrolled patients who meet all inclusion and exclusion criteria with no major protocol deviations.

All analyses will be descriptive; no hypothesis testing is planned. Continuous variables will be summarized using mean, standard deviation, median, minimum, and maximum. Categorical variables will be summarized using frequencies and percentages will be reported with their associated confidence intervals. Time-to-event data will be summarized using Kaplan–Meier curves. All data will be analyzed using SAS version 9.4, or later (SAS Institute Inc., Cary, NC).

The sample size of 500 was determined to be sufficient to accurately characterize use of WRAPSODY in real-world practice based on clinical consensus of the study’s principal investigators. An interim analysis is not currently planned.

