### Inclusion and Exclusion Criteria

The full inclusion and exclusion criteria are provided in Table 1. As this study seeks to describe the safety and efficacy outcomes associated with the use of the WRAPSODY device in a real-world population, the eligibility criteria are intentionally minimal to help capture the full range of clinical profiles of the study population and avoid bias for, or against, specific subgroups (e.g., disease states, anatomies).

**Table 1 Tab1:** Full inclusion and exclusion criteria

Inclusion criteria	Exclusion criteria
Patient provides written informed consent for study participation	Patient has a planned surgical revision of access site
Patient is male or female, with an age ≥ 18 years at date of enrollment	Patient has a known or suspected infection of the hemodialysis access site, systemic infection, and/or septicemia
Patient is willing to comply with site standard of care procedures and follow-up visit schedules over 24 months	Patient has an uncorrectable coagulation disorder
Patient is undergoing chronic hemodialysis using the hemodialysis access that the intervention will be performed upon	Known hypersensitivity to nickel titanium alloy
The dialysis access is considered mature and has been used to deliver hemodialysis treatments for at least one session	Patient's hemodialysis access is anticipated to be abandoned within 6 months
Patient has stenosis or occlusion within the dialysis outflow circuit of an AV fistula or AV graft and is treated with the WRAPSODY Cell-Impermeable Endoprosthesis System in accordance with device Instructions for Use	Patient is scheduled for kidney transplant or peritoneal dialysis within the next 6 months post-procedure
	Full expansion of a PTA balloon cannot be achieved during predilatation
	Device would be placed in the superior vena cava
	Any inflow or outflow lesion that could jeopardize patency access long-term beyond the target treatment area

AV, arteriovenous; PTA, percutaneous transluminal angioplasty

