### Follow-up

Patients will be followed for up to 24 months. During the 24 month study period, data will be collected at the following timepoints post-procedure: 30 days, 6 months, 12 months, and 24 months. Data collected will include, as available, the following: physical assessment of vascular access circuit, dialysis status, any subsequent intervention(s) on the hemodialysis access circuit, device/procedure-related adverse events (up to 6 months only), and serious device or procedure-related adverse events, including death (Table 2). Patients unable to be assessed in-person at any of the designated timepoints for data collection will be contacted by phone to confirm their status. Upon completion of the study, all patients will be treated according to routine operating practices at the institution of their hemodialysis provider.

**Table 2 Tab2:** Data collection schedule

Assessment	Baseline ≤ 30 Days	Index procedure (Enrollment)	Follow-up assessment 30 days (± 15 days) 6 months (180 ± 30 days) 12 months (360 ± 45 days) 24 months (720 ± 75 days)
Informed consent	X^a^		
Demographics	X		
Medical history	X		
Assessment of fistula or graft/access circuit	X	X	X
Dialysis status	X		X
Index procedure information^b^		X	
Subsequent interventions to access circuit			X
Device and/or procedure related serious adverse events^c^		X	X

^a^ Informed consent will be obtained for all patients prior to index procedure, or as soon as possible after the procedure but no later than time of patient discharge. Informed consent must be collected prior to any study data collection

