#### Expected Gain of Knowledge

To date, all available data published on WRAPSODY has reported excellent patency rates [19, 20]. While the positive preliminary findings related to the device are promising, there is a need for additional evidence to confirm the clinical utility of the device. The WRAP Registry study is designed to address this knowledge gap by describing the safety and efficacy outcomes associated with the device in a large and diverse patient population. As this study encompasses multiple centers globally, the results are expected to provide broad insight regarding the utility of the device that will be highly informative for healthcare decision-makers.

As patients undergoing hemodialysis typically reflect a uniquely vulnerable population with high morbidity [23, 24], there is an on-going need to continue optimizing their clinical management and provide healthcare providers with safe and effective options to extend hemodialysis access. The results from this study are expected to inform ways to continue to improve patient care. Based on the early feasibility results [20], we anticipate favorable patency outcomes with WRAPSODY relative to other currently available covered stents. The prior animal model [19] of WRAPSODY would suggest that unique design features including the integral cell-impermeable layer and softened end-rows may contribute to these patency results.

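### Kaplan–Meier is the only time-to-event method named; if death, transplant and modality change are censored, its complement would overstate the share of patients losing patency or access by 24 months

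*Protocol article*

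**What the plan says.** **Method.** The Statistics section states "Time-to-event data will be summarized using Kaplan–Meier curves" and names no other time-to-event method. It also says "All analyses will be descriptive; no hypothesis testing is planned", and for proportions "Categorical variables will be summarized using frequencies and percentages will be reported with their associated confidence intervals".

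**Outcomes.** Under Primary Outcome Measures, TLPP is lost through clinically driven revascularization, thrombosis or uncorrectable occlusion of the target lesion. Death, transplant and change of dialysis modality are not part of that event. Additional Outcome Measures Assessed presents TLPP (12 and 24 months), and access circuit primary patency and secondary patency (6, 12 and 24 months), as proportions of patients. Several are also worded as times to an event; secondary patency, for example, is "defined as the interval post-procedure until access circuit abandonment". The Abstract lists time to access abandonment as exploratory.

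**Exits from risk.** "Patients will be followed for up to 24 months". Table 1 excludes a patient under the criterion "Patient is scheduled for kidney transplant or peritoneal dialysis within the next 6 months post-procedure", which leaves unplanned exits, and those planned for months 6 to 24, open. Table 2, footnote c, has all deaths recorded throughout. Expected Gain of Knowledge describes a "uniquely vulnerable population with high morbidity".

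**Not stated.** The article does not say whether death, transplant or modality change is censored, counted as an event or treated as competing. After withdrawal, data are used up to the withdrawal date.

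**The concern.** The outcomes are described as proportions of patients, and the registry exists to describe real-world results. A patient who dies or is transplanted with a patent lesion has had no TLPP event as defined, so a default Kaplan–Meier run censors that patient. It then treats the patient as if still able to lose patency later. The complement of that curve estimates loss in a setting where nobody dies or leaves hemodialysis. The share of enrolled patients who actually lose patency is a different and smaller quantity.

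The two separate as follow-up lengthens and exits accumulate, so the 24-month figures are the exposed ones. A larger sample does not narrow the gap. Decision-makers who read the 24-month number as a patient share would carry the difference into their planning.

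**Working it through.** **The plan's own figure.** The only planning figure is the sample size of 500, set by clinical consensus without a formula: "The sample size of 500 was determined to be sufficient to accurately characterize use of WRAPSODY in real-world practice". There is nothing to reproduce, so 500 serves here only to judge precision.

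**Inputs.**
- N = 500, all enrolled and analysed together (Statistics). This is optimistic, since Study Cohort says up to 500 in two cohorts.
- 24-month loss as read from 1 − KM: L = 30% or 40% (assumed).
- Competing exits by 24 months: c = 20%, 30% or 40% (assumed). This is the share that would leave if nobody lost patency; the share that leaves first, before any loss, is lower.
- Constant, independent cause-specific hazards, and exits censored in the Kaplan–Meier analysis (assumed).

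**Formulas**, with time scaled so that 24 months = 1:
- a = −ln(1 − L) and b = −ln(1 − c)
- Cumulative incidence of loss: F = a/(a+b) × [1 − exp(−(a+b))]
- Gap = L − F
- Greenwood 95% half-width for KM: 1.96 × (1 − L) × √{ a × [exp(a+b) − 1] / [(a+b) × 500] }

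**One case in full.** L = 0.40, c = 0.20: a = 0.5108, b = 0.2231, a+b = 0.7340, exp(−0.7340) = 0.48.
- F = 0.5108/0.7340 × 0.52 = 0.362, so the gap is 3.8 points.
- Half-width = 1.96 × 0.60 × √(0.5108 × 1.0833 / (0.7340 × 500)) = 0.046.

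**All cases at 24 months.**

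| 1 − KM | Exits c | Cumulative incidence | Gap (points) | 95% half-width of KM (points) |
|---|---|---|---|---|
| 30% | 20% | 27.1% | 2.9 | 4.3 |
| 30% | 30% | 25.5% | 4.5 | 4.4 |
| 30% | 40% | 23.8% | 6.2 | 4.6 |
| 40% | 20% | 36.2% | 3.8 | 4.6 |
| 40% | 30% | 34.2% | 5.8 | 4.7 |
| 40% | 40% | 32.0% | 8.0 | 5.0 |

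**Check from the article's own patency rates.** The Introduction gives first-in-man primary patency of 97.7% at 6 months and 84.6% at 12 months. Carrying the 6-to-12-month hazard on to month 24 (an assumption) gives 1 − KM = 1 − 0.846 × (0.846/0.977)² = 36.6%. With competing exits of 5% to 25% per year (assumed):

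| Time | 1 − KM | Cumulative incidence | Gap (points) |
|---|---|---|---|
| 6 months | 2.3% | 2.3% to 2.1% | 0.0 to 0.2 |
| 12 months | 15.4% | 14.9% to 12.7% | 0.5 to 2.7 |
| 24 months | 36.6% | 34.5% to 26.6% | 2.1 to 9.9 |

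**Abandonment.** At an assumed 10% per year, 24-month 1 − KM is 19.0% against 18.1% to 14.6% (0.9 to 4.4 points). At 20% per year it is 36.0% against 34.3% to 28.0% (1.7 to 8.0 points). The exit range is the same.

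**The case against.** - **No censoring rule is stated.** A reader might infer that 24-month loss *will* be overstated. The article does not support that: it neither censors these exits nor counts them, and an analysis plan that is not shown may settle the matter. If abandonment is defined to include death, transplant or modality change, Kaplan–Meier of that composite does not have this bias. This stands, so the point is conditional.
- **Kaplan–Meier need not supply the reported figure.** Percentages with confidence intervals are also planned, and the article nowhere says that 1 − KM will be presented as the patient share. This stands too. But the long-term outcomes are worded as times to event, and this is the only method named for such data.
- **Kaplan–Meier is not wrong for lesion durability.** If exits are independent of lesion failure, censoring them estimates patency in the absence of exits, which suits comparison with published rates. A reader might infer that the curve should be replaced; it should not.
- **The direction depends on the question.** In the 40%-loss cases, the share still under observation with patency intact is exp(−(a+b)) = 48%, 42% or 36%, against a Kaplan–Meier patency of 60%. On that reading the curve overstates patency. Cumulative incidence of loss alone would not prevent the misreading, so the exits must be reported as well.
- **The stakes are limited.** The study is descriptive, the affected outcomes are secondary or exploratory, and overstated loss would work against the device. This lowers the priority but does not make the figure the right one.

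**Conclusion.** The point holds in conditional form. The article pairs outcomes worded as proportions of patients with a single time-to-event method that, applied in the standard way to the TLPP event as defined, estimates something else once patients die or leave hemodialysis. If these exits are censored and 1 − KM is read as the share affected, 24-month loss would be overstated by about 3 to 8 points for 30% to 40% loss and 20% to 40% exits. That is less than the sampling half-width of 4 to 5 points when exits are 20%, about equal to or above it at 30%, and clearly above it at 40%. At 12 months the gap is smaller, at most 2.7 points in the first-in-man scenario. The 6-month primary measure is essentially unaffected (at most 0.2 points in that scenario).

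Every exit rate, every abandonment rate and the hazard beyond 12 months is assumed, because the documents give none. The size rests on constant or piecewise constant, independent hazards. The direction needs only that the exits are censored and occur among patients who could still have the event. This is a cheap improvement to the secondary and exploratory reporting; no primary result is in error.

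**What to change.** 1. Keep the Kaplan–Meier curves, labelled as lesion or access durability in the absence of death, transplant and modality change, for comparison with published patency rates.
2. Add Aalen–Johansen cumulative incidence of TLPP loss, access circuit primary patency loss and access abandonment at 12 and 24 months. Treat death, transplant and permanent change of modality as competing events, except where the abandonment definition already counts them as events. State which applies.
3. Report the cumulative incidence of the competing events beside these figures, so that death without an event is not read as maintained patency.

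**Cost.** No new assessments appear necessary: the article already plans to record all deaths, dialysis status at each follow-up and reasons for early termination. The work is one extra set of estimates. The downside is a second set of numbers that needs explaining beside the customary curve.
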